### Sample size calculation

Using the sample size calculator available on Openepi [31] (http://www.openepi.com/SampleSize/SSPropor.htm), with an expected SARS-CoV-2 seroprevalence of 10%, an accuracy of ± 3%, an alpha risk = 5% and no design effect (Deff = 1), we need at least 384 persons in each gender and age stratum at the final round (fourth timepoint). This number has been rounded to 452 to account for approximately 85% usable data.

Therefore, considering a non-response rate of 70% at inclusion and 30% between the data collection rounds (one to four), Table 1 (below) gives the number of subjects required per age and gender group per visit. At the final round (fourth timepoint), there should be 452 for each stratum. The details of the sample size calculation are presented in Table 2.

**Table 1 Tab1:** Distribution of the city zones for the socio-anthropological study

	Bobo Dioulasso	Ouagadougou
Residential/central	1	1
Residential /peripheral	1	1
Poorer/central	1	1
Poorer/ peripheral	1	1
Total	4	4

**Table 2 Tab2:** The study sample calculation strategy

Age and gender groups	Average number of people per household	Average number of households per EA* in the study cities	Number of EA needed for the study	Estimated number of people in the selected EA	Estimated number of people to contact	Estimated number of people to select in each EA	Estimated number of people needed after round 1	Estimated number of people needed after round 2	Estimated number of people needed after round 3	Estimated number of people needed after round 4
Men and women aged 60 and over	0.15	220	160	5280	4393	28	1318	922	646	452
Men aged 19 to 59	1.26	220	160	44,352	4393	28	1318	922	646	452
Women aged 19 to 59	1.10	220	160	38,720	4393	28	1318	922	646	452
Teenagers aged 15 to 18	0.51	220	160	17,952	2152	14	0	0	646	452
Teenagers aged 10 to 14	0.61	220	160	21,472	2152	14	0	0	646	452
Total				127,776	17,483	112	3953	2767	3229	2260

*EA** Enumeration Area

To avoid the design effect (Deff = 1) in the calculation of the sample size, the sampling method will be two-stage random sampling with a probability proportional to their size in the resident population according to the data from the National Institute of Statistics and Demography survey (INSD).

To contact the 17,483 people for inclusion we will randomly choose 160 Enumeration Areas (EA) in Ouagadougou and Bobo-Dioulasso. In the two cities together 160 EA out of 1728 will be selected with a probability proportional to their size.

After selection of the EAs, the selection of individuals (second degree), will be done as follows:Complete a census and numbering of all concessions (can include several households), all households and target persons (men and women aged 60 and over, women aged 19–59, men aged 19–59, teenagers aged 15–18 and children aged 10–14 years),Number (from 1 to n) all the targeted residents by category,From each category, 28 residents will then be selected among adults and 14 teenagers from every EA.

If a selected participant is unavailable or refuses to participate in the study, he/she will be replaced with an individual randomly chosen from the same age and gender group in the same EA and in the same city. If the number of participants to select cannot be reached in an EA, it will be completed with the subsequent individuals in the randomization list. This strategy allows implicit stratification and is easy to perform. It simply requires that the sampling frame be sorted geographically before sampling systematically, with a probability to be selected proportional to the size. It also automatically provides a sample that is proportionally distributed among geographic subdivisions in the study area. Furthermore, it will make it easier to find the respondents in the field, since the interviewers will already be in touch with them through the census. Sample collection of teenagers will start at round three, enabling field investigators to obtain parental consent for their children to participate in the study during the first two rounds of data collection.

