### Statistical analysis

For the statistical analysis, this research project will adopt a dynamic approach and will constantly integrate latest knowledge emerging about COVID-19. A first analysis will be performed after the first collection on day 0, to enable important information that could be useful for the fight against COVID-19 to be relayed to the authorities in Burkina Faso.

The following analyses will be performed [7]:Calculation of the cumulative incidence by age group: i.e., the proportion of individuals who are seropositive for SARS-CoV-2 infection according to age (60 and over, 19–59 years old, teenagers aged 15–18 and children aged 10–14 years).Calculation of the cumulative incidence by gender: i.e., the proportion of individuals who are seropositive for SARS-CoV-2 infection according to gender (men, women).Serological response to infection (if the serological tests enable us to evaluate this criterion): i.e., the course of serum levels of specific antibodies against SARS-CoV-2 (increase in titers across the different measurement timepoints).Describe and compare individual, socio-economic characteristics, presence of comorbidities and exposure according to serological status of the population.

Quantitative variables will be described as mean ± standard deviation (SD) and median (range) and compared using the Student t or Mann–Whitney U tests as appropriate. Qualitative variables will be described as number and percentage and compared using the chi square or Fisher’s exact test, as appropriate.

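### Two-stage PPS sampling does not remove the design effect: the ±3 points per group is slightly optimistic, and Deff = 1 must not be carried into the phase 1 analysis

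*Protocol article*

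**What the plan says.** In the Protocol article, Phase 1, Sample size calculation, the inputs are a seroprevalence of 10%, a precision of ±3 points, a 5% alpha and Deff = 1. The conclusion is that "we need at least 384 persons in each gender and age stratum at the final round", raised to 452 to allow for about 85% usable data.

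The reason for Deff = 1 is given below Table 2, in a sentence that opens with "To avoid the design effect" and offers PPS selection in two stages as the means of doing so. The same section draws 160 of 1,728 EAs. From every EA it then selects 28 people in each adult category and 14 in each teenage category. It adds that sorting the frame geographically gives implicit stratification.

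Under The characteristics of participants, every member of a household is to be invited.

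Phase 1, Statistical analysis names Student t and Mann–Whitney tests for quantitative variables. For the rest, "Qualitative variables will be described as number and percentage and compared using the chi square" or Fisher's exact test. It mentions neither clustering nor weights, and it names no method for confidence intervals.

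**The concern.** PPS selection with a fixed take per EA makes selection probabilities roughly equal within a category. It does nothing about the fact that people in one EA, and more so in one household, share exposure to a respiratory infection. Two-stage sampling is what creates a design effect, so it cannot be the reason for setting Deff to 1.

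Two things are at stake. First, 384 is exactly the simple-random-sampling number, with no margin, so any positive net ICC takes round-4 precision in a group beyond ±3 points. Second, if Deff = 1 carries over into the analysis, the interval for the primary endpoint will be too narrow, and some comparisons by serological status will reject too often. A first analysis after day 0 is planned for relay to the national authorities, and round 1 is where the number of people per EA is largest.

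**Working it through.** **Inputs from the protocol.** p = 0.10, d = 0.03, z = 1.96, 85% usable data, 160 EAs. Table 2 gives 452 per group and 2,260 in total after round 4, and 3,953 in total (three adult groups) after round 1. **Assumed:** ICC 0.02 to 0.10, since the protocol states none.

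**The plan's own figures.** n = z²·p(1−p)/d² = 1.96² × 0.09 / 0.0009 = 384, and 384/0.85 = 451.8, so 452. Working backwards, 452/0.7 = 646, then 922, then 1,318, and 1,318/0.3 = 4,393. All of these reproduce, for a simple random sample.

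**Adding the clustering.** Deff = 1 + (m − 1)·ICC, where m is usable people per EA. Half-width = 1.96·√(Deff × 0.09/n).

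| Estimate | Usable n | m = n/160 | Half-width, Deff = 1 | Deff, ICC 0.02–0.10 | Half-width, ICC 0.02–0.10 |
|---|---|---|---|---|---|
| One Table 2 group, round 4 | 384 | 2.4 | ±3.00 | 1.03–1.14 | ±3.04 to ±3.20 |
| Pooled, round 1 | 3,953 × 0.85 = 3,360 | 21.0 | ±1.01 | 1.40–3.00 | ±1.20 to ±1.76 |
| Pooled, round 4 | 2,260 × 0.85 = 1,921 | 12.0 | ±1.34 | 1.22–2.10 | ±1.48 to ±1.94 |

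At ICC 0.20 the round-4 group figure would be ±3.39.

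**Weighting of the pooled estimate.** Table 2 takes equal numbers from unequal populations (for example 5,280 aged 60 and over, 44,352 men aged 19 to 59). With five equal groups, the weighting Deff is 5·ΣN²/(ΣN)². The populations 5,280, 44,352, 38,720, 17,952 and 21,472 give 5 × 4,277,537,792 / 127,776² = 1.31. For the three adult groups at round 1 it is 1.34. Multiplying the two components, as an approximation:
- Round 1: 1.01 × √(1.40 × 1.34) = ±1.4, up to 1.01 × √(3.00 × 1.34) = ±2.0.
- Round 4: 1.34 × √(1.22 × 1.31) = ±1.7, up to 1.34 × √(2.10 × 1.31) = ±2.2.

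All remain inside ±3 points.

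**Coverage of an interval that ignores clustering.** Approximate coverage is 2Φ(1.96/√Deff) − 1. At ICC 0.05, round 1 (Deff 2.0) gives 83% and round 4 (Deff 1.55) gives 88%, against a nominal 95%.

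**Tests.** Beta-binomial simulation: 160 EAs, prevalence 10%, 7 people per EA and group, 20,000 runs, nominal 5% test that ignores clustering.

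| ICC | Factor varying only between EAs (80 v 80) | Two groups present in every EA (e.g. men v women) |
|---|---|---|
| 0.02 | 6.4% | 5.0% |
| 0.05 | 8.9% | 4.4% |
| 0.10 | 12.3% | 3.7% |

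The error is inflated for area-level factors. For groups mixed within EAs it is about right or conservative.

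**The case against.** The best defence is that little is lost where the protocol states its target. Only about 2.4 usable people per EA and group remain at round 4, so the cost there is 0.04 to 0.20 points. Systematic selection from a geographically sorted frame may recover part of it. This stands, and it limits the size of the point. It does not make Deff equal to 1, and household correlation and uneven attrition across EAs push the other way.

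Three stronger readings are tempting but not supported.

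- A reader might infer that every planned test is too liberal. Comparisons of groups mixed within EAs are not, and many individual characteristics and comorbidities may vary mostly within EAs. Inflation depends on the factor.
- A reader might infer that the published intervals will be too narrow. The article fixes no interval method, and that may sit in a fuller document. The statement is conditional: it applies if Deff = 1 is carried into the analysis.
- A reader might take the phrase about each gender and age stratum as eight cells. With an even sex split, the three groups that pool the sexes would then have 384/2 = 192 usable people per sex, or ±4.2 points. But Table 2 and the selection steps name the same five categories, the analysis lists age and gender separately, and no sex split within the pooled groups is given. This is loose wording, not a shortfall in sample size.

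**Conclusion.** The statement that two-stage PPS sampling avoids the design effect is wrong, and the ±3 points from 384 usable people per group holds only under simple random sampling. Under the assumed ICC of 0.02 to 0.10, the effect on the stated target is small, at most about 0.2 points.

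The larger consequence is for analysis. Variances for the pooled estimate would be understated by a factor of about 1.4 to 3.0 at round 1 and 1.2 to 2.1 at round 4 from clustering alone, with roughly 1.3 more from weighting. The pooled estimate probably still meets ±3 points, so the sample is not shown to be inadequate. The tests named are anti-conservative only for factors that vary mainly between EAs. All magnitudes rest on the assumed ICC and equal numbers per EA. They make no allowance for household clustering or for any gain from implicit stratification.

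**What to change.** 1. In Sample size calculation, remove the claim that the sampling method avoids the design effect, and keep the description of the two-stage PPS selection.
2. State an assumed ICC range with its basis, and restate round-4 precision as about ±3.0 to ±3.2 points for each of the five Table 2 groups.
3. Replace the reference to each gender and age stratum with the names of those five groups.
4. In Statistical analysis, specify EA as primary sampling unit together with sampling weights. Use design-based variances for prevalences, Rao–Scott chi-square in place of plain chi-square and Fisher tests, and design-based regression in place of plain t and Mann–Whitney comparisons. The Stata and R software already named can do this.

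The cost is wording, a little analysis programming and a slightly less favourable stated precision. No extra participants are needed.

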### The characteristics of participants

A longitudinal cohort will be constituted from among the general population in the cities of Ouagadougou and Bobo-Dioulasso (Burkina Faso), which are the hardest hit by the pandemic. Households and persons will be randomly selected, with stratification by age group (60 and over, 19–59 years old, teenagers aged 15–18 and those aged 10–14 years) and gender (male, female) and included in the study. Random selection of the households will be performed based on census units of the national statistics institute of Burkina Faso. A household is considered as at least two persons living in the same dwelling, to consider so-called “celibatoriums”, which are grouped premises comprising several individual lodgings. In each household, all the members of the household will be invited to participate in the study, to collect data at days 0, 21, 42 and 63, to enable analysis by subgroup (age and gender).

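### Two-stage sampling proportional to size does not remove the design effect, so the phase 1 precision is a simple-random-sample figure and the named tests ignore clustering

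*Protocol article*

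**What the plan says.** The phase 1 section on sample size assumes 10% seroprevalence and a precision of 3 points either way, and sets the size for the last of the four rounds as follows: "an alpha risk = 5% and no design effect (Deff = 1), we need at least 384 persons in each gender and age stratum". This becomes 452 after allowing for 85% usable data. The reason given for the design effect is: "To avoid the design effect (Deff = 1) in the calculation of the sample size, the sampling method will be two-stage random sampling", with selection proportional to size. The same section draws 160 of 1,728 EAs and then, from numbered lists of residents by category, takes 28 people per adult category and 14 per teenage category in every EA. It also says the frame is sorted geographically before systematic selection.

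The section on participant characteristics describes recruitment differently: "In each household, all the members of the household will be invited to participate in the study".

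The phase 1 statistical analysis lists seropositive proportions by age and by gender, and a comparison of individual and socio-economic characteristics, comorbidities and exposure by serological status. Quantitative variables go to Student t or Mann–Whitney tests. For the rest: "Qualitative variables will be described as number and percentage and compared using the chi square" or Fisher's exact test. The section mentions no EA or household clustering, no weights and no interval method.

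**The concern.** Selection proportional to size with a fixed take per area controls who gets into the sample and with what probability. It does nothing to the similarity of people who live near each other. Two-stage selection is what introduces a design effect, so the article offers as a remedy the feature that creates the problem. For a transmissible infection there is no basis in the document for taking the ICC as zero.

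Two things are at stake. First, the 3-point precision is presented as a property of this design when it belongs to a simple random sample. Second, an analyst who accepts that the design effect has been avoided has no reason to depart from the independence-based tests in the analysis section. Some associations with serological status would then look firmer than the data allow, in a study meant to inform public policy.

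**Working it through.** **Reproducing the plan's figures.** Inputs from the sample size section: p = 0.10, d = 0.03, two-sided 5%, Deff = 1.

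- n = 1.96² × 0.10 × 0.90 / 0.03² = 384.16, so 384.
- 384 / 0.85 = 451.8, so 452.

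Both match. The arithmetic is right and the defect is the justification for Deff = 1. The 452 covers unusable data only and leaves no margin for clustering.

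**Formulas.** Deff = 1 + (m − 1) × ICC, where m is usable people per EA. Half-width = 1.96 × √(0.09 × Deff / n). The article gives no ICC, so 0.02 to 0.10 is an assumption. No gain from the geographic sort is credited.

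**Cluster sizes** (160 EAs, numbers from Table 2):

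- One stratum, round 4: 384 / 160 = 2.4.
- All five strata, round 4: 5 × 384 = 1,920; 1,920 / 160 = 12.
- One adult stratum, round 1: 1,318 × 0.85 = 1,120; 1,120 / 160 = 7.
- All adults, round 1: 3,953 × 0.85 / 160 = 21.

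**Precision.**

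| | ICC 0 | ICC 0.02 | ICC 0.05 | ICC 0.10 |
|---|---|---|---|---|
| Stratum, round 4: Deff | 1 | 1.03 | 1.07 | 1.14 |
| half-width (points) | 3.00 | 3.04 | 3.10 | 3.20 |
| usable n needed for 3 points | 384 | 395 | 412 | 438 |
| Pooled, round 4: Deff | 1 | 1.22 | 1.55 | 2.10 |
| half-width (points) | 1.34 | 1.48 | 1.67 | 1.94 |
| Adult stratum, round 1: Deff | 1 | 1.12 | 1.30 | 1.60 |
| half-width (points) | 1.76 | 1.86 | 2.00 | 2.22 |

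Only the final-round stratum estimate exceeds 3 points, and by at most 0.2 in this range.

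**If an independence-based interval were used for the pooled proportion.** Coverage = 2Φ(1.96 / √Deff) − 1. With Deff 1.22, 1.55 and 2.10, a nominal 95% interval of ±1.34 points covers about 92%, 88% and 82%.

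**Tests by serological status.** When the characteristic also varies within EAs, an approximate form is Deff = 1 + (m − 1) × ICC of outcome × ICC of characteristic. At round 1, with m = 21 and an assumed characteristic ICC of 0.05 to 0.20:

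- Low end: 1 + 20 × 0.02 × 0.05 = 1.02.
- High end: 1 + 20 × 0.10 × 0.20 = 1.40.
- True size of a 5% test = 2 × (1 − Φ(1.96 / √Deff)), so about 5% to 10%.

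For a characteristic constant within EAs, Deff is 1.40 to 3.00 and the size is about 10% to 26%. Age and gender categories are sampled inside every EA, so shared area effects largely cancel. For those comparisons the effect is weak or may reverse.

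**The case against.** The strongest defence is that little changes in practice. With 2.4 usable people per EA in each stratum, 3.04 to 3.20 points is close to the stated 3, and the pooled estimate and the round 1 adult strata stay well inside it. The geographic sort gives implicit stratification and may remove part of the variance between EAs, so the design effects above lean high for a given ICC. The article is condensed and names no interval method, and variance estimation may be set out in an analysis plan that is not shown.

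Most of this stands, and it limits the size of the point. It does not rescue the sentence itself. The sort can lower a design effect but does not justify setting it to 1. The tests are named in the article, so that part is not left open for another document.

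Three stronger readings are tempting and not supported:

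- **That the study misses its 3-point target overall.** It does so only per stratum at the last round, and slightly.
- **That coverage of the pooled interval falls to 76%.** That figure multiplies clustering by a factor of 1.31 for equal stratum sizes against the Table 2 household composition (2.10 × 1.31 = 2.75). It applies to a weighted estimate, and the article states no weights.
- **That the tests generally have 10% to 26% false positives.** This needs a characteristic nearly constant within EAs, while most of those listed are individual traits.

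Household clustering is also not established, because the detailed selection steps draw individuals from category lists.

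**Conclusion.** The claim that two-stage sampling proportional to size avoids the design effect is false as written and should be corrected. The size of 384 per stratum is valid only at zero ICC. For an assumed ICC of 0.02 to 0.10, and with no credit for the geographic sort, the final-round stratum half-width is about 3.04 to 3.20 points and the pooled round 4 half-width about 1.5 to 1.9. The sample does not need to grow.

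The analysis consequence matters more than the precision shortfall. The named tests give p-values that are too small for characteristics that cluster by EA or household, by an amount that depends on how strongly they cluster. For age and gender this is not shown. Undercoverage of about 92% down to 82% for the pooled proportion is conditional on an independence-based interval, which the article does not specify.

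**What to change.** - Delete the statement that sampling proportional to size avoids the design effect.
- Keep the sample. Restate precision using Deff = 1 + (m − 1) × ICC over a stated ICC range with its source, per stratum and pooled. If the pooled estimate is weighted to the population, carry the weighting factor as well; with 1.31 the half-width is about 1.70 to 2.23 points, still inside 3.
- In the phase 1 statistical analysis, estimate seroprevalence and compare groups with survey-design methods: EA as primary sampling unit, linearised or jackknife variance, and Rao–Scott tests or EA-clustered regression.
- Report the observed design effect.
- Reconcile the section on participant characteristics (whole households invited) with the selection steps in the sample size section (individuals drawn from category lists), because the choice changes the clustering.

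The cost is a change of wording and the use of survey procedures in Stata and R, the software already named. No participants are added. The downside is that the stated precision becomes slightly less favourable.

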### Data collection and management

Data collection in the general population will take place at four timepoints, each 21 ± 3 days apart. Blood samples will be drawn by trained and qualified personnel. In each household, the members of the household who accepted to participate will be invited to sign the informed consent form, and complete a questionnaire (Additional file 1) with socio-demographic data, comorbidities, symptoms related to SARS-CoV-2 infection and exposure, namely:Socio-demographic characteristics: age, profession, marital status, level of education, socio-professional category;Prior medical history:History of cardiovascular and thrombo-embolic disease: arterial hypertension, rhythm disturbances, cardiomyopathy, deep venous thrombosis, pulmonary embolism;History of metabolic diseases: diabetes mellitus, kidney failure;History of pulmonary disease: tuberculosis, asthma, chronic obstructive pulmonary disease (COPD);Other relevant medical history.Lifestyle habits: tobacco and alcohol consumption;Clinical signs of COVID-19: fever (temperature ≥ 38 °C), cough, dyspnea, etc.;Exposure to COVID-19: any contact with a confirmed case of COVID-19.

Persons who complete the questionnaire will be requested to give a blood sample to extract serum for the assessment of SARS-CoV-2 antibodies. Venous blood samples will be collected at the four different timepoints (Days 0, 21, 42, 63) to enable analysis in the laboratory. Blood will be collected by venous puncture performed by health workers within the participant’s home. In total, 4 ml of blood will be drawn in a 5 ml EDTA tube for each participant, at each timepoint.

The blood samples will be transported to the laboratory within 6 h of the collection, along with the relevant follow-up sheet for the blood samples. For transport to the laboratory, blood samples will be triple packed in an isotherm container containing an icebox to preserve the cold chain.

All blood samples will be analyzed in the Laboratory of the MURAZ center in Bobo-Dioulasso. Laboratory procedures involving handling of blood samples will be performed in a class 2 biosafety cabinet. For blood samples collected in the city of Bobo-Dioulasso, samples will be sent to the laboratory daily. Samples from Ouagadougou will also be sent daily to the laboratory of the national center for research and training on malaria in the same city where they will treated.

At the laboratory, plasma samples will be centrifuged and aliquoted within 12 h of the blood collection. If the time to preparation (centrifugation and aliquoting) is likely to exceed 12 h, it will be temporarily stored at + 4 °C for up to a maximum of 72 h. To minimize the number of freeze–thaw cycles [7], two (2) aliquots of 1 ml plasma each will be prepared from each blood sample. One of these will be used for the serological tests by ELISA anti-SARS-CoV-2 for both IgM and IgG. For participants who consent to conservation of their blood samples, the second aliquot will be stored at −80 °C in a secure biobank at the laboratory of the MURAZ center in Bobo-Dioulasso, in case needed for quality control, additional tests or future research.

Laboratory tests will use the WANTAI SARS-CoV-2 Ab ELISA, an Enzyme-Linked Immunosorbent Assay (ELISA) intended for qualitative detection of total antibodies (including IgG and IgM) to SARS-CoV-2 in human serum and Acid Citrate Dextrose (ACD) plasma. The WANTAI SARS-CoV-2 Ab ELISA is intended for use as an aid in identifying individuals with an adaptive immune response to SARS-CoV-2, indicating recent or prior infection. Before being used in this study, the assays will be validated for the Burkinabe context on a small series of characterized samples from Burkinabe patients (10 positive and 10 negative samples by PCR).

The results of the biological analyses and the questionnaire data will be recorded in an electronic case report form (CRF), which will be secured by personal access codes for each researcher. Data will be transferred to the data management center at the MURAZ center daily, after preliminary data checks by the supervisors in the field. Data will be cleaned and tested for coherence and completeness, and aberrant values will be identified. Queries generated in case of aberrant data will be sent to the research supervisors in the field to be resolved by the researchers before the end of data collection.

The database will be locked after the data has been cleaned and all queries have been resolved. The database will then be exported for statistical analysis.

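### Phase 1 draws blood into EDTA tubes, but the protocol describes the ELISA as intended for serum and ACD plasma and nowhere says that EDTA plasma is acceptable

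*Protocol article*

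**What the plan says.** All the relevant statements stand in the protocol article, Phase 1, Data collection and management.

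- Purpose of the draw: participants are "requested to give a blood sample to extract serum for the assessment of SARS-CoV-2 antibodies".
- Tube: 4 ml of blood is collected in a 5 ml "EDTA tube for each participant, at each timepoint".
- Laboratory preparation: "plasma samples will be centrifuged and aliquoted within 12 h of the blood collection", and two "aliquots of 1 ml plasma each will be prepared from each blood sample".
- Specimen tested: "One of these will be used for the serological tests by ELISA anti-SARS-CoV-2 for both IgM and IgG".
- Assay: the ELISA is described as intended for qualitative detection of "total antibodies (including IgG and IgM) to SARS-CoV-2 in human serum and Acid Citrate Dextrose (ACD) plasma".
- Check before use: the assay is to be validated locally on a small series, "10 positive and 10 negative samples by PCR". The specimen type of that series is not given.

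The Phase 1 Study endpoints section makes the proportion of the population with specific antibodies the primary endpoint. This ELISA is the only assay the protocol names for measuring it.

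**The concern.** The protocol fixes the tube, names the specimen and states the assay's intended use, and the three do not agree. An EDTA tube holds an anticoagulant, so it yields EDTA plasma, which is neither serum nor ACD plasma. Because the protocol states these details, and states them inconsistently, this is not a matter of an article leaving laboratory detail to a fuller document.

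At stake is the measurement behind the primary endpoint. If the assay behaved differently in EDTA plasma, the change in sensitivity or specificity would pass directly into the estimated seroprevalence, overall and in every age and gender group. The Phase 1 Statistical analysis section also plans a first analysis after the day 0 collection, to inform the authorities, so any such error would reach decision-makers early.

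**Working it through.** **1. Can the statements be read together?**

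| Step | Specimen implied |
|---|---|
| Purpose of the draw | Serum |
| Tube | EDTA plasma |
| Laboratory preparation and testing | Plasma, anticoagulant not named |
| Assay's stated intended use | Serum or ACD plasma |

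Three readings might reconcile them.

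- *The tested specimen is serum.* Blood in an EDTA tube does not clot, and the laboratory text says plasma.
- *The tested specimen is ACD plasma.* ACD is a different anticoagulant, and the protocol's abbreviation list expands ACD and EDTA separately.
- *A second tube supplies the assay.* None is mentioned; the 4 ml in the EDTA tube is given as the total drawn at each timepoint.

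None works, and no statement in the protocol says that EDTA plasma is acceptable for this assay.

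**2. How many samples are affected?** Inputs are the Table 2 totals of people needed after rounds 1 to 4, taking one draw per person per round:

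3,953 + 2,767 + 3,229 + 2,260 = 12,209.

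The tube is specified for every participant at every timepoint, so this is the whole Phase 1 sample set.

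**3. Could the planned validation settle it?** With n correct out of n, the two-sided 95% exact (Clopper-Pearson) lower limit is 0.025^(1/n). For n = 10:

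0.025^(1/10) = 0.692.

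A perfect result in the positives is thus compatible with a sensitivity as low as about 69%, and likewise for specificity in the negatives. Even if the series were EDTA plasma, it could not exclude a material specimen effect.

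**4. Does the sample size depend on this?** No. The stated figures reproduce: 1.96² × 0.10 × 0.90 / 0.03² = 384.1 (stated 384), and 384 / 0.85 = 451.8 (stated 452). The choice of tube changes neither.

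**5. How would an accuracy shift act?** The documents give no sensitivity or specificity for this assay in any specimen, so the values below are assumptions, for illustration only. Apparent prevalence = p × Se + (1 − p) × (1 − Sp), with p = 10%, the seroprevalence expected in the sample size section.

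| Se (assumed) | Sp (assumed) | Calculation | Apparent prevalence |
|---|---|---|---|
| 100% | 98% | 0.100 + 0.90 × 0.02 | 11.8% |
| 100% | 95% | 0.100 + 0.90 × 0.05 | 14.5% |
| 90% | 100% | 0.090 + 0 | 9.0% |
| 80% | 100% | 0.080 + 0 | 8.0% |
| 90% | 97% | 0.090 + 0.90 × 0.03 | 11.7% |

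The error can go either way, and losses of sensitivity and specificity partly offset each other.

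**The case against.** The strongest case on the other side accepts the textual mismatch but holds that it shows only an inconsistent description. The intended-use sentence does not say that other plasma types are unsuitable. The kit insert is not among the documents, and the slip could lie in the tube name or in the assay description. A validation before use is planned and may well be run on the study specimen. All of this stands. It limits the point to a contradiction that must be resolved and rules out any claim of demonstrated bias.

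A reader might infer three stronger things that the documents do not support.

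- *That a 3-point loss of specificity would consume the ±3% precision.* At 10% prevalence and 90% sensitivity it gives 11.7%, a net error of +1.7 points; reaching +3 would need a loss of 0.04 / 0.90 = 4.4 points. Even at 100% sensitivity, 3 points add 2.7, and the full 3 needs 0.03 / 0.90 = 3.3 points. The ±3% is moreover a sampling precision per stratum and not a tolerance for bias, and no loss of any size is documented.
- *That the kit's accuracy figures were obtained in other specimen types.* The protocol gives no such figures and does not say on what specimens any were established.
- *That the problem could not be repaired later.* The stored second aliquot does come from the same EDTA tube. But blood is drawn at four rounds, so paired EDTA plasma and serum from a subsample at a later round could measure a specimen effect and at least partly correct earlier results.

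What the objection does not remove is that the protocol, as written, puts every sample outside the use it states for its own assay. The planned validation does not answer that: it names no specimen type and is too small.

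**Conclusion.** The point holds as an internal contradiction about the specimen for the primary endpoint. It affects all of the roughly 12,209 planned samples, assuming one draw per person needed at each round of Table 2. It rests on the assay's intended use as the protocol describes it; whether the manufacturer also accepts EDTA plasma cannot be settled from these documents.

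There is no evidence here that EDTA plasma gives wrong results, and the size and direction of any bias are unknown. The planned 10 + 10 validation, with an exact lower limit of about 69% at best, would not give that reassurance. The matter is worth settling before fieldwork because it covers every measurement of the endpoint and takes little to resolve at that stage.

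**What to change.** Before fieldwork, make the tube, the named specimen and the assay indication agree, by one of two routes.

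1. Use a tube that yields serum or ACD plasma, so that the specimen is one the protocol lists for the assay. This needs no extra visit or draw.
2. Keep EDTA and document that EDTA plasma is acceptable for this assay. One way is to run the planned validation on paired EDTA plasma and serum from the same people, and to report the agreement with its confidence interval. This costs a few extra validation specimens. As ten per group gives wide limits, the number of pairs should be chosen for the precision wanted. If acceptability is already documented elsewhere, citing it and correcting the assay description would be enough.

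Under either route, state the specimen type of the validation series and use one specimen term throughout Phase 1, including the Statistical analysis section, which refers to antibody levels in serum.
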